## Abstract

**Background:**

Fussy eating is most often a developmentally typical behaviour, generally presenting during toddlerhood. However, up to half of parents of young children are concerned about fussy eating, and this concern may mediate the use of nonresponsive feeding practises, such as coercive or unstructured feeding and using food to reward eating. Despite the high prevalence of parental concern for fussy eating and the negative impacts nonresponsive feeding practises have on children’s health and diets, no previous digital intervention to improve the feeding practises of parents of toddlers concerned about fussy eating has been evaluated.

**Aim:**

This article describes the protocol of a randomised controlled feasibility pilot aiming to evaluate Fussy Eating Rescue, a purely web app based intervention for parents of toddlers. The primary aim is to investigate feasibility and acceptability; secondary aims are to explore indications of intervention effect on parents’ feeding practises or children’s eating behaviours.

**Methods:**

Fussy Eating Rescue features include: (1) a Tracker, that allows parents to track repeated offers of food, (2) Topics, providing information on fussy eating, effective feeding strategies, and general nutrition, (3) Rescues, containing quick references to material supporting Topics contents, (4) Recipes, and (5) SMS notifications. Parents of toddlers (12–36 months old, *n* = 50) who have concerns about fussy eating will be recruited via Facebook. Parents will be randomised to an intervention group, which receives access to the app for 6 weeks, or to wait-listed control. Outcomes will be assessed at baseline and 6 weeks after app use, using online questionnaires and app usage statistics. Primary outcomes include participant retention rate, intervention engagement, app usability, perceived ease in using the app, perceived usefulness of the app, and user satisfaction. Secondary outcome measures include parents’ feeding practises and children’s eating behaviours.

**Discussion:**

Results will inform whether Fussy Eating Rescue is a feasible way to engage parents concerned for their toddler’s fussy eating behaviours. If feasible and acceptable to users, a larger trial will further examine the efficacy of the Fussy Eating app in improving parents’ feeding practises and children’s eating behaviours.

**Trial registration:**

Prospectively registered with the Australian New Zealand Clinical Trials Registry on 15 July, 2021 (ACTRN12621000925842).

## Background

The parent–child feeding relationship is fundamental to early childhood development [1]. Parent–child feeding interactions have important bonding, socialization, and learning opportunities for children and are a key influence of young children’s diet quality [2]. Responsive feeding practises that support children’s autonomy to eat in response to their development and physiological needs have been shown to have positive impacts on children’s diet and health [3, 4]. In contrast, nonresponsive feeding practises—such as coercive feeding (e.g. pressuring to eat, coercive rules), unstructured feeding (e.g. allowing child to graze during the day), and using food to reward eating—have negative impacts on children’s’ ability to attend to internal signals of hunger and satiety and contribute to poor dietary outcomes and the development of long-term unhealthy eating preferences, i.e. low intakes of nutrient-dense foods (e.g. vegetables, fruits, whole grains) and high intakes of discretionary foods (e.g. savoury and sweet snacks, desserts, sugar-sweetened beverages) [3, 4]. In the long-term, poor diets are associated with the development of non-communicable diseases, including diabetes and heart disease, stroke and cancer, hypertension, non-alcoholic fatty liver disease, and poor bone health [5]. Previous longitudinal and cross-sectional research suggests that nonresponsive feeding practices are commonly used by parents who describe their child as a “fussy” or “picky” eater [6–13]. Fussy eating is variably defined as eating a limited variety or amount of food, having strong food preferences, or rejecting foods that are unfamiliar, have specific textures, or are in particular groups or categories [14]. While the lack of a clear definition for fussy eating makes estimating its prevalence problematic [15–17], studies have reported that up to 50% of parents of children 2–5 years are concerned about fussy eating [9, 18–20] and parents concern for fussy eating is a primary mediator of parents’ use of nonresponsive feeding practices [9, 18–20].

Fussy eating most commonly begins in early toddlerhood (12 to 24 months) and peaks in intensity in later toddlerhood (24 to 36 months) [21, 22]. The evidence suggests that most toddlers described as ‘fussy eaters’ by their parents are likely exhibiting developmentally typical eating behaviours that are likely to resolve as children age [20]. However, nonresponsive feeding practises may increase the intensity of and duration of fussy eating behaviours [9–12]. Therefore, targeted interventions that addresses parents’ concerns for their toddlers’ fussy eating behaviours are warranted.

Parents of young children have expressed a preference to engage digitally with health promotion content [23, 24]. An important advantage of digital health interventions is that they allow participants to access content at any time and any place of their choosing, which may mitigate barriers related to transportation, childcare, and scheduling conflicts [25–27]. Using digital platforms also provides opportunities to tailor content so that it is perceived to be personally relevant to the user [28]. Further, digital health interventions may also have advantages related to cost [29, 30] and scalability [25].

Previous digital parent feeding interventions have shown promise in improving parents feeding practices [31, 32]; however, no digital intervention has been developed to improve the feeding practises specifically among parents of toddlers concerned for fussy eating. Given the high proportion of parents concerned about fussy eating [8, 18–20], evidence that underlying fussy eating may undermine child nutrition interventions [33], and the general need for effective, scalable parent-centred feeding interventions [34], the development of successful interventions among this population is warranted.

The primary aim of this study is to assess the acceptability and feasibility of Fussy Eating Rescue, a fully-automated web app that aims to improve the feeding practises of parents concerned for toddler fussy eating behaviours. Primary feasibility measures include assessing participant retention rate, intervention engagement, app usability, perceived ease in using the app, perceived usefulness of the app, and user satisfaction. A secondary aim is to explore any indications of intervention effect.

## Methods

### Design

This protocol describes a 6-week, two-arm, parallel, randomised control pilot trial to evaluate a purely web app based intervention to improve the feeding practises of parents of toddlers (12–36 months) who are concerned for their toddler’s fussy eating behaviours. Parents assigned to the intervention group will have access to the web app containing information, strategies, recipes, and activities to track feeding attempts. Parents in the intervention group will also be able to opt into receiving to 42 SMS messages across the 6 weeks with tips and prompts to revisit the app. Pre and post-measures collected from a control group of parents (placed on a six week waitlist) will be used to evaluate indications of intervention effect. The description of the protocol and intervention are in line with the CONSORT guidelines for randomised pilot and feasibility trials [35]. A CONSORT diagram is provided in \* MERGEFORMAT Fig. 1 and the CONSORT checklist. The trial is prospectively registered at the Australian New Zealand Clinical Trials Registry (ACTRN12621000925842) and ethics approval was obtained from Deakin University Human Research Ethics Committees (2021–139).

**Fig. 1 Fig1:**
[figure not shown]
CONSORT diagram for the randomised controlled pilot study evaluating the feasibility of Fussy Eating Rescue

### Study sample and recruitment

Parents who self-identify as concerned for the fussy eating behaviours of their toddler (12–36 months old) will be recruited via paid Facebook advertisements. The Facebook advertisement audience settings will be used to target adults (18–45 years) living in Australia who have general interests related to parenting toddlers. To address a common issue of study recruitment involving the overrepresentation of participants with relatively high socioeconomic position, a geographic location parameter will also be used to preferentially show advertisements to Facebook users who live in postcodes in the lower 2 deciles of the Socio-Economic Indexes for Areas (SEIFA), a product developed by the Australian Bureau of Statistics that ranks Australian areas based on measures of relative socio-economic advantage and disadvantage [37]. Participants will be eligible for inclusion if they currently live in Australia, are able to read and write in English, have a mobile phone that can access the internet and care for a child who is 12–36 months old and lives with them at least half of the time. The intervention has been developed to address the concerns of parents whose children display developmentally typical eating behaviours and have no co-existing conditions that present additional nutritional risk. Given this, participants will be excluded if they indicate that their child has been diagnosed with autism spectrum disorder, learning difficulties, avoidant/restrictive intake disorder, or a medical condition that requires them to follow special dietary requirements (e.g. type 1 diabetes, cystic fibrosis, celiac disease, or metabolic conditions).

Individuals who click on the Facebook ads will be taken to a REDCap screening survey hosted at Deakin University [38]. Eligible participants will be provided with a written introduction to the study and a plain language statement outlining the study protocols before providing informed consent.

Informed by evidence from the literature on sample size requirements for pilot RCTs, it is estimated that a sample of 40 participants will generate sufficient data to determine the feasibility of the intervention [39, 40]. To allow for a potential 20% attrition rate, a total of 50 participants will be recruited.

Participants will be randomised to either the Fussy Eating intervention or a wait-listed control group (25 participants in each group). The allocation sequence generation will be completed via the REDCap randomization module. Due to the wait-list design, participants will be aware of whether or not they are receiving an intervention, and this study will be non-blinded.

Intervention.

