#### Intervention delivery

Participants in the intervention group will be sent an email with instructions for how to access the intervention app to their personal smartphone. The email will contain a link to the webpage where the web app is hosted, their username, and a temporary password. Participants will be required to set a new password the first time they access the app. Parents will be instructed to either (1) place a bookmark to the web app on their phone’s home screen or (2) install the web app to their phone, which will deliver a ‘native-like’ experience to participants.

Across the 6 weeks of the intervention, participants will receive SMS messages that contain feeding tips and links to the app, prompts to reengage with the app, and summaries of their activities on the app (e.g. summary of food offers tracked that week). In line with the evidence that personalised, tailored information supports behaviour change interventions, the SMS messages will be tailored to each participant based on child’s age, current feeding practises, feeding goals, and their own preferences (e.g. time of day, day of week, frequency).

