### Analysis

Analysis of primary outcomes, related to feasibility and acceptability, will only be available from the intervention group and therefore cannot be blinded. Analysis of secondary outcomes, which will be collected from intervention and control participants, will be blinded. Data will be analysed with R [65] using RStudio software [66]. Frequencies and proportions will be calculated for categorical data; means and standard deviations will be calculated for continuous data; medians and IQRs will be calculated for ordinal data. Descriptive statistics derived from usage data will be used to characterise the engagement and acceptability of the intervention app. Specifically, building upon previous research conducted by the research team, an engagement index will be calculated from five subindices: click depth, loyalty, interaction, recency, and feedback [67, 68]. Although this pilot RCT will not be powered to detect intervention effects, the within-group mean differences and 95% CIs will be reported for changes in secondary intervention outcomes between baseline and 6 weeks. The standardised mean differences between intervention and control groups will be interpreted as 0.2 = small effect, 0.5 = moderate effect, 0.8 = large effect, and 1.2 = very large effect [69].

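### The between-arm comparison of secondary outcomes is planned as a labelled standardised difference with no adjustment or interval described, although baseline scores and child age will be in hand

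*Protocol article*

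**What the plan says.** The protocol article, under Study sample and recruitment, starts from 40 participants ("it is estimated that a sample of 40 participants will generate sufficient data to determine the feasibility of the intervention") and inflates this: "To allow for a potential 20% attrition rate, a total of 50 participants will be recruited", with "25 participants in each group". On the method of allocation it says "The allocation sequence generation will be completed via the REDCap randomization module". It names no stratification factor and excludes none.

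The Background gives the age course: "Fussy eating most commonly begins in early toddlerhood (12 to 24 months) and peaks in intensity in later toddlerhood (24 to 36 months". Eligibility runs from 12 to 36 months, so it covers both phases.

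The Analysis section concedes the limits of the effect aim ("Although this pilot RCT will not be powered to detect intervention effects"). It then fixes two things for the secondary outcomes. The first is the change from baseline within each arm, with 95% CIs. The second is the comparison of arms: "The standardised mean differences between intervention and control groups will be interpreted as 0.2 = small effect", with further labels at 0.5, 0.8 and 1.2. It describes no interval for that comparison and no covariate, and does not say whether it uses change scores or 6-week scores.

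Under Secondary outcomes, every scale is measured both before and after the intervention. Under Demographics, child age is reported at baseline.

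**The concern.** The secondary aim is to look for indications of effect, and only the comparison between arms bears on it. As described, the uncertainty is attached to the wrong quantity. Each arm's own change gets an interval, while the difference between arms gets a verbal label.

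In a sample of 40 to 50, the arms will differ by chance in starting score and, for the child outcomes, in age. Both are measured before the intervention, so the part of the noise they explain can be removed. If it is left in, a label of small or moderate effect (or of none) may partly reflect who happened to be allocated where. The labels could then colour the planning of the larger trial, which is to examine the same kinds of outcome.

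**Working it through.** **Plan's own figure.** 40 / (1 − 0.20) = 50, or 25 per arm, and 20 per arm after the planned attrition. This reproduces. The 40 rests on cited pilot-trial literature, so there is no power formula to check.

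**Chance error of the SMD with no true effect.** SE ≈ √(2/n per arm).
- 25 per arm: √(2/25) = 0.283; 95% range ±1.96 × 0.283 = ±0.55.
- 20 per arm: √(2/20) = 0.316; 95% range ±0.62.
- Chance of |SMD| ≥ 0.2: 48% and 53%. Chance of |SMD| ≥ 0.5: 7.7% and 11.4%.

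**Part due to one baseline covariate.** If a covariate correlates r with the outcome, its chance imbalance shifts the SMD with standard deviation r√(2/n). Adjusting for it leaves an SE of √(2/n) × √(1 − r²). The documents give no r, so all values are assumed.

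| r | 95% range of shift, 25 / 20 per arm | Chance of a shift ≥ 0.2, 25 / 20 | Chance of \|SMD\| ≥ 0.2 after adjustment, no effect, 25 / 20 |
|---|---|---|---|
| 0.1 | ±0.06 / ±0.06 | under 0.1% / under 0.3% | 48% / 53% |
| 0.3 | ±0.17 / ±0.19 | 1.8% / 3.5% | 46% / 51% |
| 0.5 | ±0.28 / ±0.31 | 16% / 21% | 41% / 47% |
| 0.6 | ±0.33 / ±0.37 | 24% / 29% | 38% / 43% |

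**Child age.** The upper two rows (0.1 to 0.3) are the plausible ones for age, because six weeks is short and change scores remove stable differences in level. The shift is then ±0.06 to ±0.19.

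**Baseline score.** The same scale measured six weeks apart should correlate more strongly than age does, so the lower rows are a fair illustration if the SMD is on 6-week scores. If it is on change scores, let ρ be the correlation between baseline and 6 weeks, with equal variances σ². The outcome variance is 2σ²(1 − ρ) for change and σ²(1 − ρ²) for the baseline-adjusted model. The ratio of adjusted to change is (1 + ρ)/2. At an assumed ρ of 0.5 it is 0.75, so the SE falls to √0.75 = 0.87 of the change-score SE; at 0.6 it is 0.80, and √0.80 = 0.89. Baseline adjustment helps whichever score is meant.

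**Age imbalance under allocation without strata.** Assume half the children are 24 months or older. By the hypergeometric distribution, the arms differ by 20 percentage points or more in the share of older children with probability 0.26 (25 per arm) or 0.34 (20 per arm), and by 28 points or more with probability 0.09 (25 per arm). If the age bands differ by an assumed 0.5 SD (range 0.25 to 0.75), a 20-point imbalance shifts the SMD by 0.20 × 0.5 = 0.10 (0.05 to 0.15) and a 28-point imbalance by 0.28 × 0.5 = 0.14 (0.07 to 0.21).

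**The case against.** A reader might infer that the trial ignores child age and that age imbalance could therefore pass for an intervention effect. The documents do not support that, for several reasons.

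- The article is silent on strata and covariates, and silence is not a decision. A condensed article may leave both to a fuller protocol or analysis plan.
- The age shifts worked out above (0.10 to 0.14 SMD) stay below the 0.2 label. Only the extreme corner, 0.28 × 0.75 = 0.21, reaches it, and the difference between age bands has no source in the documents.
- Age is a minor part of the chance error. A 0.5 SD difference between equal bands corresponds to r = 0.5/√(0.5² + 4) ≈ 0.24. Removing it entirely lowers the chance of |SMD| ≥ 0.2 under no effect only from 48% to about 47% (25 per arm).
- The stated age course concerns child fussiness. Nothing similar is given for the six feeding-practice measures. Recruiting only parents already concerned may also weaken the age contrast in this sample.
- Tailoring SMS content to age ("the SMS messages will be tailored to each participant based on child’s age, current feeding practises, feeding goals, and their own preferences") is a feature of the intervention and creates no chance difference between arms.
- Feasibility and acceptability are assessed in the intervention arm only, so imbalance between arms cannot bias them.

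All of this stands. It does not answer the narrower point: the article does state how the arms will be compared, and a better estimate is available from data already collected. Being unpowered is a reason to show the interval for the comparison, since a label alone hides how wide it is.

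**Conclusion.** The point holds as a modest improvement to an exploratory analysis. It is not an error that threatens the trial. The described comparison leaves avoidable noise in the SMD and describes no measure of its uncertainty, although that uncertainty is about ±0.55 to ±0.62 under no effect. Baseline score is the main source of gain. Child age is secondary, about ±0.06 to ±0.19 SMD under an assumed correlation of 0.1 to 0.3, and is relevant to the child outcomes only. Adjustment does not make the labels reliable: even at an assumed r of 0.6, an SMD of 0.2 or more would appear with no effect in 38% to 43% of such pilots. The interval is therefore as important as the covariates. The case for an age-stratified allocation is weak.

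**What to change.** For each secondary outcome, estimate the between-arm difference at 6 weeks from a linear model with arm and the baseline score. Add child age as a covariate for the two child outcomes, CEBQ Food Fussiness and the MBQ. Report the adjusted difference with its 95% CI beside the standardised difference, and state which score the standardised difference is based on. If an analysis plan not shown here already does this, a sentence in the article saying so is enough.

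The cost is one or two degrees of freedom: with 40 completers, 38 residual degrees of freedom become 37 or 36. No new data or participants are needed. Stratifying allocation by child age is optional and not required; small blocks within strata would also make allocations easier to predict in a non-blinded trial.

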### *I*ntervention content

#### App development overview

Development was completed in three phases: (1) Ground, (2) Design, (3) Build and Test. This paper describes the protocol for the final phase: (4) Pilot (Fig. 2).

**Fig. 2 Fig2:**
[figure not shown]
Development phases for Fussy Eating Rescue as it aligns with the IDEAS (Integrate, Design, Assess, and Share) frame work [36], adapted for iterative co-design activities

#### Grounding in theory and previous research

A systematic, evidence-based approach was used to develop the Fussy Eating Rescue mHealth intervention using the Theoretical Domains Framework [41], Behavior Change Wheel (BCW) [42], and Behavior Change Techniques Taxonomy v1 (BCTTv1) [43]. This process was informed by researchers’ formative qualitative studies among the intended users of *Fussy Eating Rescue* [44] and consultation of the existing literature related to fussy eating and parent feeding practices in the toddler years [45]. Per the BCW, the researchers first identified the problem in behavioural terms, i.e. that parents concerned their toddler’s fussy eating behaviours were using nonresponsive feeding practices. The target behaviours were feeding practices identified in the literature as helpful versus problematic in the context of fussy eating. Responsive behaviours to promote included: repeated exposure (exposing children repeatedly to a wide variety of healthful foods, even those they have previously refused) [22, 46, 47], family meals [48], role modelling [49, 50], and meal and snack routines [51, 52]. Nonresponsive practices to discourage included pressure [11, 53], catering (offering children alternative foods when initial foods are rejected or offering a limited number of foods per child’s current taste preferences [7, 8, 11, 51, 54], and using food to reward eating or good behavior [7, 11].

Qualitative research previously undertaken by the research team [44, 55] and studies highlighted by a recent systematic review and synthesis of previous qualitative studies examining fussy eating [45] were consulted to compile a list of barriers and facilitators to using responsive feeding practices. Facilitators included: self-efficacy beliefs [44, 45], focusing on long-term outcome goals for their child’s eating behaviours [44] ability to self-regulate emotions and behaviours [44], knowledge that fussy eating is common and developmentally normal [44, 45, 55] knowledge of how children develop food preferences [44, 45, 55], and knowledge of what feeding practices are effective and ineffective [44, 45, 55]. Barriers included: parent concern about fussy eating (e.g. inadequate nutrient/energy intake, food waste, child going hungry, behavioural issues related to food refusal) [45, 48, 56], distrust in children’s hunger regulation [45], and attributing fussy eating to behavioural issues [45].

